### 9.3 Sample Size

The current trial is designed detect a shift on the modified Rankin Scale score, which represents the global disability, to a lower score. The expected distribution of the modified Rankin Scale score, derived from the EVT for acute anterior circulation ischemic stroke (ACTUAL) registry and the Highly Effective Reperfusion evaluated in Multiple Endovascular Stroke Trials (HERMES) collaboration, is as follows: 7%, 20%, 16%, 11%, 13%, 8% and 25%.

The sample size was calculated using the cumulative proportion of patients with mRS 0-2. We assume a moderate effect of 7% absolute increase in the cumulative proportion of patients with mRS 0-2 in the intervention group, compared with controls, indicating an odds ratio (OR) of 1.33, which have substantially exceeds the minimal clinically important difference. In order to demonstrate the expected

treatment effect with a type-1 error  $\alpha = 0.05$  (two-tailed) and a power of 80% ( $\beta = 20\%$ ). A sample size of  $n = 1588$  patients ( $n = 794$  per treatment group) is required.

The intention-to-treat principle will be applied to the primary analysis and, therefore, to safeguard against dilution of the treatment effect associated with an approximate 5% non-adherence rate (due to loss to follow-up, consent withdrawal and other reasons), we initially planned to enrol  $n = 1672$  patients ( $n = 836$  per treatment group) for this study. This estimation was performed based on PASS (NCSS, LLC, Kaysville, Utah, USA) version 15.0.

## **10. Imaging Training**

Investigators involved in image reading within the trial will participate in a standardized image reading training before study start.

## **11. Randomization**

Randomization will be done by a web-based APP (Jinlingshu) on mobile phone or computer (<https://jinlingshu.com/>). The automated system will assign an appropriate set of study medication to each patient. Eligible patients are randomized to treatment with either intravenous methylprednisolone or placebo with a ratio of 1:1.

Randomization will be stratified by participating centre with permutation block size of 4. Randomization will be completely concealed by having both web-based real-time allocation and identical appearance of methylprednisolone sodium succinate and placebo bottles. (All bottles will have a unique number. Subjects will be assigned a

random serial number according to the time they were enrolled, and corresponding masked medications will be provided).

The randomization list will be prepared by the independent statistical centre using SAS 9.4. It will only be sent to the data coordination centre responsible for central randomization and data management, the pharmacy centre responsible for treatment packaging.

## **12. Blinding/Unblinding**

Both patient and investigator are blinded to treatment assignment. If there is a clinical situation that the investigator believes it is necessary to unblind for the safety of patients, the medical monitor must be immediately notified to discuss the intended unblinding. Premature breaking of the blind should be restricted to the setting where identification of the type of treatment is critical for adequate treatment of the patient. All unblinded patients will remain in the study and complete all follow-up visits.

If the site principal investigator wants to know the identity of the study drug for any other reason, he or she must call the medical monitor. Unless the circumstances are deemed necessary by site principal investigator, treatment codes should not be broken. The site principal investigator should document and make an explanation for any premature unblinding.

For the purpose of regulatory reporting, if required by the local health authorities, treatment codes could be broken for all serious, unexpected suspected adverse reactions that are deemed by the investigator to be related to study drug.

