## **16. Assessment**

## **16.1 Assessment of efficacy**

### **16.1.1 The modified Rankin Scale (mRS)**

The mRS score is a valid and reliable clinician-reported measure of global disability that has been widely applied for evaluating recovery from stroke. It is a scale used to measure functional recovery (the degree of disability or dependence in daily activities) of people who have suffered a stroke. mRS scores range from 0 to 6, with 0 indicating no residual symptoms; 5 indicating bedbound, requiring constant care; and 6 indicating death. The mRS score will be obtained at

Day 90. Premorbid mRS status will also be obtained retrospectively and reported on the 24 Hours CRF page. In this trial, we will keep video and voice recording versions of mRS score except those who die, unable, or refuse to take a video. For mRS score at Day 90, the mRS score will be assessed by two independent certified neurologists in a blinded manner with the video combined with voice record. For those who decline to participate in a video recording, the outcomes will be determined in person by site neurologists blinded to the treatment assignment, and keep a chat record with site neurologists. Disagreements are resolved by consensus.

The mRS will only be scored by those who have been trained and certified to use this scale using the table below. (See appendix 1)

[figure not shown]

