#### **16.2.4 Proportion of patients with gastrointestinal bleeding.**

The statistical analysis of differences in proportions of patients with gastrointestinal bleeding within 7 days between Methylprednisolone and Placebo groups will be performed. Gastrointestinal bleeding will be reported by local investigators.

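### Section 12 limits code breaks to clinical need, then lets the site principal investigator break the code for other reasons on that person's own judgement

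*Supplement*

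**What the plan says.** All references are to protocol version 2.0.

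- **Section 12, first paragraph.** Patient and investigator are blinded. If the investigator thinks unblinding is needed for safety, the medical monitor must be told at once and the intended break discussed. The limit is explicit: "Premature breaking of the blind should be restricted to the setting where identification of the type of treatment is critical for adequate treatment". Unblinded patients stay in follow-up.
- **Section 12, second paragraph.** This covers the site principal investigator who "wants to know the identity of the study drug for any other reason". That person must call the medical monitor. The condition on the break itself is: "Unless the circumstances are deemed necessary by site principal investigator, treatment codes should not be broken". Afterwards, "The site principal investigator should document and make an explanation for any premature unblinding".
- **Section 12, third paragraph.** Codes may also be broken for regulatory reporting of serious unexpected suspected reactions.
- **Section 11.** Allocation is 1:1, web-based and "stratified by participating centre with permutation block size of 4". The list goes only to the data coordination centre and the pharmacy centre, and bottles look identical.
- **Section 16.1.1.** Two independent certified neurologists score day-90 mRS, blinded, from video and voice records. For patients who decline video, "the outcomes will be determined in person by site neurologists blinded to the treatment assignment".
- **The two sections numbered 16.2.4.** Local investigators report pneumonia, against listed criteria. For the other steroid harm, "Gastrointestinal bleeding will be reported by local investigators".
- **Sections 16.2.7 and 16.2.8.** The investigator assesses causality of adverse events.
- **Sections 16.2.2 and 7.2.5.** Symptomatic intracranial haemorrhage is adjudicated by an independent imaging core laboratory and the Clinical Events Committee. That committee also validates complications and grades their severity and relatedness.

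**The concern.** The second paragraph of section 12 applies, by its own terms, to reasons other than those in the first. On a literal reading the person who asks for the code also decides whether the request is good enough. The call to the monitor is a notification, and the written explanation comes after the code is known. Neither is stated as a control that could stop the break.

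What is at stake is the part of the data that sites themselves produce: local reporting of pneumonia and gastrointestinal bleeding, the investigator's causality judgement, and the mRS of patients who refuse recording. A second, smaller effect comes from section 11. The block size is fixed, is the same at every centre, and is printed in the protocol, so each code learned at a site carries some information about other patients in the same block, including any not yet enrolled.

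**Working it through.** **1. The two rules side by side**

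| | First paragraph | Second paragraph |
|---|---|---|
| Trigger | Patient safety | Any other reason |
| Test | Treatment identity critical for adequate treatment | Site principal investigator deems it necessary |
| Medical monitor | Notified at once, to discuss | Must be called; no approval or veto stated |
| Record | Explanation for any premature unblinding | Same |

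If the first paragraph's limit governs every premature break, the second paragraph has nothing left to permit. If the second paragraph permits anything, it permits breaks that the first rules out. One of them has to give way.

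**2. What one broken code says about block-mates**

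The plan states no figure on this point, so there is none to reproduce. Inputs from section 11 are the 1:1 ratio and the fixed block of 4 within centre. A block holds two of each arm in one of 6 equally likely orders.

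- *No break:* best guess for any patient is right 50% of the time.
- *One break:* three places remain, two of them in the opposite arm. P(a given block-mate is opposite) = 2/3 = 66.7%. None of the three is determined.
- *Two breaks in one block:* the second is in the same arm as the first with probability 1/3. Only then are the other two patients determined. Otherwise they are one of each arm and the guess is back to 50%.
- *Three breaks in one block:* the fourth patient is determined.

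The 66.7% assumes that the site can tell where a block starts. Centre is the only stratifier stated and a site knows its own enrolment order, so counting in fours is plausible, though the protocol does not say whether sites can do this. If the boundary is unknown and the broken code is equally likely to be in any position, an adjacent patient shares the block with probability 3/4, so P(opposite) = 3/4 × 2/3 + 1/4 × 1/2 = 62.5%.

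**3. Scale per centre**

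Section 7.1 gives 82 centres, and the planned total is 1672. 1672/82 = 20.4 patients, and 20.4/4 = about 5 blocks per centre on average.

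**4. Effect of a larger block**

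P(opposite after one break) = (B/2)/(B − 1): 0.667 for B = 4, 0.600 for B = 6, 0.571 for B = 8. A larger block weakens the clue but does not remove it.

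**5. Which outcomes a break can reach**

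- *Open in part:* locally reported pneumonia and gastrointestinal bleeding, investigator causality, and mRS for patients who decline video.
- *Protected:* mRS scored from recordings by independent blinded neurologists, and symptomatic haemorrhage adjudicated away from the site.

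**The case against.** The strongest reply is that section 12 is awkward English rather than a loophole. The sentence in dispute is a default prohibition, the first paragraph can be read as limiting every premature break, the monitor must be called, and each break must be explained in writing. No site-held code is described. This softens the point, because a careful site would probably follow the first paragraph. It does not dispose of it: the second paragraph names other reasons as its subject and gives no test beyond the requester's view.

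The outcome safeguards are also real. The fallback mRS rater is required to be blinded, so on the text someone who has learned the code should not rate. The Clinical Events Committee validates complications and grades relatedness, pneumonia has listed criteria, and mortality is objective. What stands is narrower. Section 12 does not say how a site's fallback rater is kept unaware once the site's own principal investigator knows the code, and nothing in section 7.2.5 shows that the committee would find events that a site did not report.

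A fixed block of 4 is not an error in a double-blind trial with concealed central allocation. It matters here only because it adds to what a permitted break reveals.

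Three stronger readings are tempting and not supported:

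- *That each break exposes the neighbouring patients.* One break determines nobody.
- *That a third of allocations become certain.* The calculation (1 + 1/3)/4 = 33% certain, with (0.5 + 0.667 + 0.667 + 1)/4 = 70.8% guessed correctly, requires every earlier assignment in the block to be known. Section 12 does not bring that about.
- *That steroid hyperglycaemia makes the problem worse.* It is a possible clue whatever the code-break rule says. The stopping rule in section 17.2 applies to both arms, and section 9.2 excludes only glucose above 22.2 mmol/L on the high side, so a high value alone does not identify the arm.

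**Conclusion.** The contradiction in section 12 is real, is in the current version, and should be removed. As written, the protocol permits unblinding for non-clinical reasons on the sole judgement of the person who asks.

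The consequence is limited. A break is fully informative about one patient and moves each block-mate from 50% to 66.7% (62.5% for an adjacent patient if block boundaries are unknown). Certainty about others needs two same-arm breaks or three breaks within one block. The outcomes open to influence are the locally reported harms, the investigator's causality calls and the fallback mRS.

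A reader might infer that the blind fails at the sites and that the primary result is compromised. The documents do not support that. The main mRS route and symptomatic haemorrhage are assessed independently of the site, and neither the frequency of code breaks nor the share of patients declining video is given, so no bias can be computed. This is a cheap improvement, not a threat to the trial's validity.

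**What to change.** 1. **Section 12.** Delete the second paragraph's route for other reasons, or make any such request subject to approval by the medical monitor or another unblinded person independent of the site. Codes would then be broken, without that independent approval, only on the first paragraph's criterion or for regulatory reporting. Leave the first paragraph's safety route exactly as it is, with no new authorisation step in front of it.
2. **Sections 12 and 16.1.1.** State that anyone who has learned a patient's code does not rate that patient's day-90 mRS, and that the existing central raters are used wherever a recording exists. For patients who refuse recording, central scoring is not available, so a site neurologist who does not know the code still has to rate.
3. **Section 11.** Use randomly varying block sizes that are not disclosed to sites, and take the block size out of the protocol that sites hold.

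The cost is wording in three sections and a setting in the randomisation system. Investigators lose discretion for non-clinical unblinding. Possible within-centre imbalance grows slightly: the most a single incomplete block can leave is half its size, so 2 patients with blocks of 4, 3 with blocks of 6 and 4 with blocks of 8.

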## **13. Study Treatment**

### **13.1 Formulation, Packaging, and Handling**

Methylprednisolone sodium succinate and its placebo are manufactured by Lummy Pharmaceutical Group Co., Ltd., Chongqing, China. All study medication will be manufactured, tested, released, and shipped according to Good Manufacturing Practice guidelines. Labelling and packaging of study medication will be conducted according to Good Clinical Practice and Good Manufacturing Practice guidelines, and any national regulatory requirements.

Methylprednisolone sodium succinate and its corresponding placebos are provided in numbered and are visually identical, except for a unique number. Methylprednisolone sodium succinate and its placebo will be packed in glass bottle of identical appearance. Each kit has a unique identification number and will be stored in a safe location at room temperature on the clinical site with limited access.

### **13.2 Test Product**

Each kit of the methylprednisolone group contains 12 bottles, and each bottle contains 40mg methylprednisolone sodium succinate, labelled for “Study Drug” and “clinical trial use only”). Each kit will be stored in a safe location at room temperature (25°C with excursions permitted between 15°C–30°C) on the clinical site with restricted access.

### **13.3 Comparator**

Each kit of the placebo group contains 12 bottles, and each bottles contains 40mg placebo, labelled for “Study Drug” and “clinical trial use only”). Each kit will be stored in a safe location at room temperature (25°C with excursions permitted between 15°C–30°C) on the clinical site with restricted access.

### **13.4 Dosage, Administration, and Compliance**

Eligible patients will be randomly assigned a number corresponding to a blinded sealed medication kit that sent to each patient. It is recommended to start using the study drug within 15 minutes after randomization.

#### **13.4.1 Methylprednisolone and its Placebo**

Patients will be assigned to receive either a placebo or methylprednisolone, with a dosage of 2mg/kg (based on estimated or actual weight if known, not exceeding a maximum dose of 160 mg) per day for a duration of 3 days. The initial study drug will be administered as soon as possible after randomisation. It is recommended that the initial study drug administrated before arterial access closure, but it should not be delayed more than 2 hours after arterial access closure. All patients will be treated according to the current Chinese Stroke Association guidelines for clinical management of cerebrovascular disorders. Risk factors such as diabetes mellitus, hypertension, hyperlipidaemia, hyperhomocysteinaemia, obesity, drinking and smoking should be managed appropriately.

#### **13.4.2 Concomitant therapy**

Administration of any other (intravenous or oral) corticosteroids (E.g.,

Hydrocortisone) is not allowed during the first 72 hours post randomization.

Gastrointestinal prophylaxis and hyperglycemia treatment will be administered per standard local protocols. Any concomitant medication within one week prior to screening through the study completion/discontinuation visit should be documented in the Concomitant Medications Case Report Form.

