#### GENERAL

Increased dosage of rapidly acting corticosteroids is indicated in patients on corticosteroid therapy who are subjected to any unusual stress before, during, and after the stressful situation.

Results from one multicenter, randomized, placebo-controlled study with methylprednisolone hemisuccinate, an intravenous corticosteroid, showed an increase in early (at 2 weeks) and late

(at 6 months) mortality in patients with cranial trauma who were determined not to have other clear indications for corticosteroid treatment. High doses of systemic corticosteroids, should not be used for the treatment of traumatic brain injury.

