**Endocrine**

Hypothalamic-pituitary adrenal (HPA) axis suppression, Cushing's syndrome, and hyperglycemia. Monitor patients for these conditions with chronic use.

Corticosteroids can produce reversible HPA axis suppression with the potential for glucocorticosteroid insufficiency after withdrawal of treatment. Drug induced secondary adrenocortical insufficiency may be minimized by gradual reduction of dosage. This type of relative insufficiency may persist for months after discontinuation of therapy; therefore, in any situation of stress occurring during that period, hormone therapy should be reinstituted.

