## 9.2 Exclusion Criteria

Patients meeting any of the following criteria will be excluded from study enrolment.

- Intracranial hemorrhage confirmed by cranial computed tomography (CT) or magnetic resonance imaging (MRI);
- mRS score  $\geq 2$  before onset;
- Pregnant or lactating women;
- Allergic to contrast agents;
- Allergic to glucocorticoids;
- Participating in other clinical trials;
- Systolic blood pressure  $> 185$  mmHg or diastolic pressure  $> 110$  mmHg, and oral antihypertensive drugs can not control;
- Genetic or acquired bleeding constitution, lack of anticoagulant factors; Or oral anticoagulants and INR  $> 1.7$ ;
- Blood sugar  $< 2.8$  mmol/L (50 mg/dl) or  $> 22.2$  mmol/L (400 mg/dl), platelet  $< 90 \times 10^9/L$ ;
- The artery is tortuous so that the thrombectomy device cannot reach the target vessel;
- Bleeding history (gastrointestinal and urinary tract bleeding) in recent 1 month;

- Chronic hemodialysis and severe renal insufficiency (glomerular filtration rate < 30 ml/min or serum creatinine > 220 umol/L [2.5 mg/ dL]);
- Life expectancy due to any advanced disease < 6 months;
- Follow-up is not expected to be completed;
- Intracranial aneurysm and arteriovenous malformation;
- Brain tumors with imaging mass effect;
- Severe systemic infectious diseases.

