#### **14.1 Screening period (Visit V0, Randomization)**

##### **14.1.1 Visit V0**

For each eligible patient, written informed consent for participation in the study will be obtained from the patient or the patient's legal representative prior to the performance of any protocol-related investigation. Once written informed consent is obtained, the results of the following standard of care assessments will be used for the study. The investigator will record the details of all patients consented to confirm eligibility and record the reasons for screening failure.

- Demographics
- Medical history
- Physical examination
- Determination of the pre-stroke mRS via interview of the patient or the patient's kin
- NIHSS score (Note: performed by an NIHSS-certified practitioner)
- Collection of information on previous medications
- Measurement of blood pressure and heart rate
- Pregnancy test (urine test, in non-menopausal women)

- Laboratory tests
- A 12-lead ECG
- Non-contrast CT scan or MRI scan and CTA, MRA, or DSA
- Concomitant medications
- Checking of inclusion and exclusion criteria

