#### **14.1.2 Randomization (R)**

If all inclusion criteria are met and no exclusion criteria are present, randomization will be performed.

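### Patients on, or recently withdrawn from, systemic corticosteroids are eligible, yet Section 13.4.2 bars other intravenous or oral corticosteroids for 72 hours with no stated exception, which the protocol's own product warnings contradict

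*Supplement*

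**What the plan says.** All references are to protocol version 2.0.

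- **Eligibility.** The one steroid-related item in Section 9.2, and in the synopsis, is "Allergic to glucocorticoids". Section 14.1.2 makes the listed criteria decisive: "If all inclusion criteria are met and no exclusion criteria are present, randomization will be performed".
- **Medication history.** Visit V0 (Section 14.1.1) includes "Collection of information on previous medications". No look-back period is given there, and no eligibility rule uses the information. Section 13.4.2 asks for concomitant medication from one week before screening.
- **The ban.** Section 13.4.2 concerns "Administration of any other (intravenous or oral) corticosteroids", gives hydrocortisone as its example, and ends: "Hydrocortisone) is not allowed during the first 72 hours post randomization". It states no exception for maintenance, replacement or stress use.
- **Study drug.** Under Section 13.4.1 one arm receives methylprednisolone daily for 3 days and the other receives placebo.
- **Product warnings.** Section 6.4, General: "Increased dosage of rapidly acting corticosteroids is indicated in patients on corticosteroid therapy who are subjected to any unusual stress". Section 6.4, Endocrine, says that relative adrenal insufficiency can last for months after treatment ends, and that "in any situation of stress occurring during that period, hormone therapy should be reinstituted". The Endocrine paragraph under Precautions repeats this.

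**The concern.** The three parts of the protocol cannot all be followed for one identifiable kind of patient: someone who takes a systemic corticosteroid at stroke onset, or who stopped one recently enough for adrenal suppression to persist. A large-vessel stroke treated by thrombectomy is hard to read as anything other than unusual stress. The eligibility list admits the patient, the product section says that corticosteroid is indicated, and Section 13.4.2 forbids it from any source other than the study drug. In the active arm the study drug is itself a corticosteroid. In the placebo arm nothing takes its place.

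What is at stake is first the safety of those individuals, and second whether a site can tell from the protocol what it is permitted to do.

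**Working it through.** **Step 1. Can such a patient be randomised?** Yes. Section 9.2 and the synopsis list only allergy, and Section 14.1.2 randomises anyone who meets the listed criteria. V0 may reveal the medication, but nothing follows from it.

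**Step 2. Does the ban apply to that patient?** Yes, for the intravenous and oral routes. Inhaled and topical use are not named. The 72 hours run from randomisation and apply in both arms, and no exception is written.

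**Step 3. Who is left uncovered?** The ban is the same in both arms, but the 3 days of study drug span the same period and contain a corticosteroid in one arm only. The uncovered patients are therefore mainly on placebo. An active-arm patient whose study drug is stopped early could also be uncovered, because the ban is not tied to study-drug status.

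**Step 4. Does the product text address these patients?** Yes. The General warning covers patients on corticosteroid therapy under stress. The two Endocrine paragraphs cover stress in the months after withdrawal.

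**Step 5. Does another section lift the ban?**

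| Section | What it allows | Lifts the 72-hour ban? |
|---|---|---|
| 12 | Emergency unblinding; the patient stays in follow-up | Not stated |
| 17.1 | The investigator may withdraw a patient for safety | Not stated |
| 17.2 | Study drug is stopped if continuing is harmful; follow-up goes on | Not stated |
| 19.1 | General commitment to best treatment | Not stated |

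**Step 6. How many patients?** The plan's arm size reproduces. Section 18.1 gives control mRS 0-2 as 7% + 20% + 16% = 43%, against 50% with treatment, at two-sided alpha 0.05 and 80% power. The unpooled normal formula gives

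n = (1.960 + 0.842)² × (0.43 × 0.57 + 0.50 × 0.50) / 0.07² = 793.06, so 794 per group, and 794 / 0.95 = 836.

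The documents give no prevalence of corticosteroid use, so the share below is an assumption:

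| Assumed share | Of 1672 in all | Of 836 on placebo |
|---|---|---|
| 0.5% | 8.4 | 4.2 |
| 1% | 16.7 | 8.4 |
| 2% | 33.4 | 16.7 |
| 5% | 83.6 | 41.8 |

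The working range is 0.5% to 2%, or about 4 to 17 placebo patients. The 5% row shows how the count would grow if recently withdrawn patients made the share larger.

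**Step 7. How far could the result move?** Take an extreme case on the mRS 0-2 cut used for the sample size. Suppose 43% of the affected placebo patients would otherwise have reached mRS 0-2 and every one of them failed to. The placebo proportion would fall by 0.43 × 0.5% = 0.2 points to 0.43 × 2% = 0.9 points, against a planned difference of 7 points. Any realistic shift would be smaller.

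**The case against.** The other side has four serious arguments.

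1. **Safeguards exist.** A site that needs to know the allocation can unblind under Section 12, and Sections 17.1, 17.2 and 19.1 put the patient's safety first. This disposes of one tempting inference, that the blind leaves the site with no means of finding out who is uncovered. It does not close the gap, since a site that has unblinded a placebo patient still faces a prohibition with no exception.
2. **Section 6 is a product summary, not a set of conduct rules.** That is right, and general prescribing advice there should not be read as trial procedure. But the sponsor chose to include the stress and withdrawal warnings, and they bear directly on patients whom Section 9.2 admits. It is fair to say that the passages are unreconciled.
3. **The numbers are unknown and probably small.** This stands. A reader might infer that harm on placebo would pass for a benefit of methylprednisolone and so bias the trial. The documents do not support that: they give neither the number of such patients nor any rate of harm, and Step 7 shows little room for it.
4. **Anaphylaxis is not a second instance.** A reader might link the ban to anaphylaxis as a stopping reason in Section 17.2 and to drug hypersensitivity among the indications in Section 6.2. But Section 6.2 confines that indication to severe allergic conditions that have failed conventional treatment, and Section 6.3 contraindicates the product in known hypersensitivity to it. The text does not carry that extra claim.

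**Conclusion.** The gap is real and follows from the protocol's text alone. Patients on, or recently withdrawn from, systemic corticosteroids are eligible. They are barred from other intravenous or oral corticosteroids for 72 hours, and they are the subject of warnings in the same document that point the other way. No section expressly resolves this.

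Confidence is high about the missing provision. It is low about the size, which rests wholly on the assumed 0.5% to 2%. The case for acting rests on the safety of a few individuals and on a contradiction that sites cannot resolve for themselves. It does not rest on bias in the primary analysis, and a sensitivity analysis that leaves out so few patients would add little.

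**What to change.** The sponsor should reconcile the exclusion list (Section 9.2 and the synopsis), Section 13.4.2, and the General and Endocrine warnings of Section 6.4 with the Precautions, so that they agree for patients on or recently withdrawn from systemic corticosteroids. Whether this is done through the eligibility list or through the wording of Section 13.4.2 is for its medical team. No clinical rule is proposed here.

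Either route must cover both groups. A change that addressed only current users would leave the recently withdrawn eligible and still barred. The medication history at V0 therefore needs a stated look-back long enough to capture recent withdrawal. None is stated now, and the one-week window in Section 13.4.2 is too short for an effect that Section 6.4 says may persist for months.

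The cost is a short amendment with ethics approval under Section 20.4, and one more question in the V0 history. If the eligibility route is chosen, the number of candidates lost would be about 8 to 33 for every 1672 at the assumed share.
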